### Multiple testing

There will be no formal adjustment for multiple comparisons. Outcomes are clearly categorised by degree of importance (primary and secondary) and cover a broad range of disciplines (e.g. behavioural, psychological, ethical, economic). Subgroup analyses have been pre-specified and are based on strong rationale and behaviour change theory.

### Summary of study data

Descriptive statistics will be prepared to summarise the data distributions and the characteristics of the study participants by allocation group. Continuous variables will be summarised using: *n* (non-missing sample size), mean (SD), median (25th–75th centiles) and categorical variables will be summarised by frequency and percentages (based on the non-missing sample size) of the observed levels.

### Subject disposition

Subject disposition will be summarised with a Consolidated Standards of Reporting Trials (CONSORT) Flow Diagram (see Supplementary Figure 2).

### Demographic and baseline variables

A list of baseline measures for all participants are shown in Supplementary Table 1.

### Intervention compliance

We will document the number of people who completed the different aspects of the intervention, including providing a saliva sample, successful genotyping, receipt of booklets and a phone call from the genetic counsellor.

### Efficacy analyses

Efficacy analyses will be conducted on the basis of ‘intention to treat’. All group comparisons will be two-tailed with a nominal 5% significance level, and will adjust for baseline scores and randomised stratification factors [40]. For (secondary) efficacy analyses that involve the pooled two-phenotype risk groups, the model will also include phenotypic risk (high, low).

### Primary efficacy analysis

Geometric mean score and 95% CI will also be represented graphically from over time (baseline, follow-ups 1 and 2). The primary analysis will be an intention-to-treat comparison of intervention and control arms for mean differences in UVR exposure measured as log-transformed daily SEDs at 12 months. The primary efficacy of the intervention will be assessed in each phenotypic risk group (high and low). UV dosimeter values will be log-transformed because of their right-skew distribution, and log-transformed values will be interpreted as a percentage change in the geometric mean of SEDs/day [41]. An analysis of covariance (ANCOVA), adjusted for baseline values and all randomised stratification factors will be performed [40]. A sensitivity analysis will be conducted on the subgroup of participants (*N* = ~ 240) that will wear a UV dosimeter for 10 days at follow-up 1 (see subheading 'Sensitivity Analysis'); given the repeated nature of the outcomes in this subgroup, generalised linear mixed models (GLMMs) with random intercepts will be fitted to assess the overall intervention effect. The primary analysis will be based on the complete case principle given that the power was adjusted with a conservative loss to follow-up rate of 15%. However, if 10% or more of the randomised patients do not have their primary outcome recorded, a sensitivity analysis will be performed using multiple imputation methods assuming that data are missing at random.

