### Outcome measures

#### Primary outcome measure

The primary outcome for this study is total daily Standard Erythemal Doses (SEDs) measured 12 months after the baseline assessment (baseline questionnaire and UV dosimeter). A SED is an objective measure of UV exposure, measured using a time-stamped electronic dosimeter badge, mounted in light-weight, custom-made wristbands attached to the left wrist (similar to wearing a watch) during daylight hours [16]. UV dosimetry is the gold standard for assessing personal UV exposure [17, 18]. UV dosimeters will be worn by all participants for 10 days at baseline, and again 12 months after baseline. A subgroup of ~ 240 participants will also wear a UV dosimeter 1 month after receipt of the booklet/s. Total daily SEDs will be calculated as the weighted average of the average daily weekday and weekend SEDs (i.e. (weekday× 5 + weekend× 2)/7). SED values will be log-transformed for all analyses.

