### Randomisation and blinding

Randomisation occurred once participants had completed their baseline questionnaire and returned their baseline UV dosimeter. Randomisation to the intervention or control arm (allocation ratio 1:1) was conducted independently by the University of Sydney’s NHMRC Clinical Trials Centre Randomisation Service using a computer-based system. The stratified minimisation procedure [35] was used to ensure that the study groups were balanced by:
Traditional phenotypic risk score (low vs. high) [36],Sex (male vs. female),State or territory of residence within Australia, andAge group (18–44 years vs. 45–69 years)

Traditional risk scores were classified as high or low based on a validated published risk prediction model that includes variables for moles (naevi), hair colour, eye colour, artificial sunbed use, first-degree family history of melanoma, and personal history of keratinocyte cancers (e.g. basal cell carcinoma, squamous cell carcinoma) [36]. For the traditional risk score, a cut-point of 1.223 was used to ensure that approximately half of participants were in the low/high-risk groups; this cut-point is based on data from our pilot trial and Australian Melanoma Family Study controls) [13, 36].

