### Sample size

Sample size calculations are based on detecting a 20% difference in the primary outcome of average daily SEDs between intervention and control arms, in each of the low- and the high-risk phenotype groups. There is currently no consensus as to a ‘safe’ daily SED limit. Instead, skin cancer prevention strategies for the public primarily aim to shift the distribution of sun exposures downwards, especially in seasons of peak exposure. Due to the skewed nature of the SED exposure data, the sample size was calculated using a *t* test with a geometric mean ratio (geometric mean SEDs in intervention group/geometric mean SEDs in control group) of 0.8, coefficient of variation 0.9, 80% power and *α* of 0.05.

Based on these calculations, a sample of 756 people (378 in the high-risk phenotype group and 378 in the low-risk phenotype group), split evenly between the intervention and control arms, will provide 80% power to detect a 20% reduction in the primary outcome in favour of the intervention with either low- or high-risk phenotypes. Allowing up to 15% with incomplete follow-up at 12 months, we will need to recruit 892 people (446 in each of intervention and control arms). Secondary analysis pooling the data from the low- and high-risk phenotype groups will give > 97% power to detect a 20% difference in SEDs between the intervention and control groups.

No interim analysis, safety analysis and or data monitoring is planned for this study due to the minimal risks associated with the intervention.

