### Sensitivity analysis

A sensitivity analysis of the repeated measures UV dosimeter data will be conducted on the subgroup of participants (*N* = ~ 240) who wear a UV dosimeter at 1 month and 12 months, using GLMMs with random intercepts to account for the repeated measures.

A sensitivity analysis will also be completed comparing the results for people who completed follow-up in the spring/summer of 2018/2019 vs. 2019/2020 due to the bushfires experienced in Australia during the latter period and the potential impact on personal and ambient UV exposure.

A sensitivity analysis will be conducted in which dosimeter data will be used to adjust for the effects of measurement error in the relative-risk estimate for self-reported sun exposure, using established methods [43].

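### Adding time of year of baseline dosimeter wear to the primary ANCOVA would gain a modest amount of precision at negligible cost

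*SAP article*

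**What the plan says.** The SAP (Primary efficacy analysis) compares log-transformed daily SEDs at 12 months within each phenotypic risk group: "An analysis of covariance (ANCOVA), adjusted for baseline values and all randomised stratification factors will be performed". The stratification factors are listed under Randomisation and blinding: phenotypic risk, sex, age group and "State or territory of residence within Australia". The pooled secondary analysis adds phenotypic risk (Efficacy analyses). None of these is a calendar term.

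On timing, the Primary outcome measure section states: "UV dosimeters will be worn by all participants for 10 days at baseline, and again 12 months after baseline". Exposure is "measured using a time-stamped electronic dosimeter badge", so wear dates are held. Randomisation followed return of the baseline dosimeter.

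Calendar time comes up in two other places. The Sample size section says that public prevention strategies aim to "shift the distribution of sun exposures downwards, especially in seasons of peak exposure". The Sensitivity analysis section plans an analysis "comparing the results for people who completed follow-up in the spring/summer of 2018/2019 vs. 2019/2020", because of the bushfires and "the potential impact on personal and ambient UV exposure".

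**The concern.** Time of year is a plausible source of variation in personal UV dose. It is available from the device and, for the baseline wear, cannot be affected by allocation. A prognostic covariate of that kind can usually be added to an ANCOVA cheaply, and the gain is a narrower interval for the primary comparison in both phenotype groups.

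Baseline SED is a same-season measurement, but it does not do this job fully. It enters with a single slope that has to serve season, stable personal habit and short-term noise together. The noise pulls the slope below 1, so the part of season that recurs at 12 months is under-corrected. What is at stake is efficiency, not validity.

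**Working it through.** **Reproducing the plan's figures (Sample size section).** Inputs: geometric mean ratio 0.8, coefficient of variation 0.9, two-sided alpha 0.05, 80% power, 15% incomplete follow-up.

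- Log-scale SD = sqrt(ln(1 + 0.9²)) = 0.7703; difference = |ln 0.8| = 0.2231.
- The two-sample t test (noncentral t) needs 189 per arm per phenotype group, with power 0.802. 4 × 189 = 756, as stated.
- 189/0.85 = 222.4, rounded up to 223; 4 × 223 = 892, as stated.
- Pooled, 378 per arm: power 0.978, consistent with the stated figure of over 97%.

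The sample size is correct. It rests on an unadjusted t test and takes no credit for baseline.

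**Model for the gain.** The SAP gives no seasonal share and no correlation, so both are assumed. Scale log SED to variance 1 at each wave. Let s be the share due to season, identical at both waves; p the share due to the stable person; and the rest independent noise. Then:

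- Correlation, and hence baseline slope: rho = s + p, which is below 1 whenever there is noise.
- Residual variance with baseline only: v0 = 1 − rho².
- Residual variance with baseline and season: v1 = (1 − s) − (rho − s)²/(1 − s).
- Difference: v0 − v1 = s(1 − rho)²/(1 − s). This is positive unless s = 0 or rho = 1.

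Example, s = 0.20 and p = 0.30, so rho = 0.50: v0 = 1 − 0.25 = 0.750; v1 = 0.80 − 0.09/0.80 = 0.6875; reduction = 0.0625/0.750 = 8.3%.

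Power below is per phenotype group with 189 per arm, log-scale SD 0.7703 × sqrt(v0) or 0.7703 × sqrt(v1). Variance explained by the stratification factors is ignored.

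| rho | s | v0 | v1 | Reduction | Power, before to after | Interval narrower by |
|---|---|---|---|---|---|---|
| 0.5 | 0.05 | 0.750 | 0.737 | 1.8% | 0.900 to 0.905 | 0.9% |
| 0.5 | 0.10 | 0.750 | 0.722 | 3.7% | 0.900 to 0.911 | 1.9% |
| 0.5 | 0.20 | 0.750 | 0.688 | 8.3% | 0.900 to 0.923 | 4.3% |
| 0.5 | 0.30 | 0.750 | 0.643 | 14.3% | 0.900 to 0.939 | 7.4% |
| 0.7 | 0.05 | 0.510 | 0.505 | 0.9% | 0.976 to 0.977 | 0.5% |
| 0.7 | 0.10 | 0.510 | 0.500 | 2.0% | 0.976 to 0.978 | 1.0% |
| 0.7 | 0.20 | 0.510 | 0.488 | 4.4% | 0.976 to 0.980 | 2.2% |
| 0.7 | 0.30 | 0.510 | 0.471 | 7.6% | 0.976 to 0.983 | 3.9% |

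At rho = 0.3 the reduction runs from 2.8% to 23.1%. The upper end has s = 0.30 and therefore p = 0, meaning no stable personal component at all, so it should be read as an extreme.

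**Cost.** With about 370 residual degrees of freedom per phenotype group, two extra terms inflate the variance by about 370/368 = 1.005, or 0.5%. That is below the smallest reduction in the table (0.9%).

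**The case against.** The strongest reply is that the SAP contains no error here. Baseline plus stratification factors is a standard adjustment set, treatment is randomised, and the two wear periods are a year apart by design. State or territory, a rough proxy for latitude, is also in the model. All of this stands, and it is why the remaining gain is small.

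Four stronger readings are tempting, and the document supports none of them.

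- *The 12-month estimate is biased by season.* A reader might infer this from the missing term. Leaving out a prognostic covariate in a randomised comparison of log means costs precision but does not bias the estimate.
- *The primary tests have only 80% power and need the help.* The 80% belongs to the unadjusted t test. At rho = 0.5 the planned ANCOVA already has about 0.90 per phenotype group.
- *The SAP itself treats season as a strong source of variation among participants.* The remark "especially in seasons of peak exposure" describes public prevention strategies, and no variance share is given. The bushfire comparison concerns a difference between years, which terms in day of year cannot capture.
- *The 1-month dosimeter comparison is confounded by calendar date*, since that visit is timed from booklet receipt. The SAP gives no delivery lag by arm and does not say whether control booklets were timed to match. The actual 1-month date also falls after randomisation, so adjusting for it would not be clearly safe.

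The figures are also a best case. They assume that the seasonal component repeats from year to year and is fully captured by one sine and cosine pair across all states. The sensitivity section refers to follow-up in spring/summer. It does not say that all wear fell there, but if it did, s would be small and the gain would sit at the low end.

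**Conclusion.** The point holds as a modest, nearly free improvement in precision. The primary and pooled models omit a covariate that is recorded, fixed before randomisation, and only partly represented by baseline SED. The further reduction in residual variance is about 2 to 14% at rho 0.5 and 1 to 8% at rho 0.7, over assumed seasonal shares of 0.05 to 0.30. Primary intervals would narrow by roughly 0.5 to 7% over the same range. The direction does not depend on the assumed values as long as some seasonal variance recurs and baseline is noisy. The size does, and it cannot be established from the SAP. The planned analysis remains valid without the change.

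**What to change.** Before database lock, extend the covariate list of the primary and pooled ANCOVA with: time of year of baseline dosimeter wear (sine and cosine of day of year). Use the baseline date and not the actual 12-month wear date, which falls after randomisation. Keep the planned 2018/2019 versus 2019/2020 comparison for the year effect. If the team prefers not to alter the primary model, name the extended model now as a supporting analysis, since adding season after the outcome data are known would be a post hoc choice.

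The cost is one line of SAP text and two degrees of freedom out of about 370 per phenotype group. No new data are needed.

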### Secondary efficacy analyses

Where outcomes were assessed at three time points (baseline, 1 month, 12 months), including most questionnaire items, data will be analysed using GLMMs with random intercepts for continuous outcome measures, and generalised estimating equations (GEEs) with a log link function for binary outcome measures to estimate relative risks. The GLMM and GEE approach allows us to account for correlation due to repeated measures on each individual [42]. Where outcomes were assessed at two time points only (baseline and 12 months), data will be analysed using ANCOVA for continuous outcome measures [40], and using GLM with log link function for binomial outcome variables to estimate relative risks and 95% CIs. The mean difference and 95% CIs between intervention and control groups at 12 months will be estimated.

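### A random intercept alone forces equal residual variance at 1 and 12 months, so the 12-month intervals for continuous secondary outcomes are miscalibrated unless those variances happen to be equal

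*SAP article*

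**What the plan says.** The section Secondary efficacy analyses sets the scope: "Where outcomes were assessed at three time points (baseline, 1 month, 12 months), including most questionnaire items". For these outcomes "data will be analysed using GLMMs with random intercepts for continuous outcome measures", and the reason given is that "The GLMM and GEE approach allows us to account for correlation due to repeated measures on each individual". The reported quantity is a single-visit contrast: "The mean difference and 95% CIs between intervention and control groups at 12 months will be estimated". By Table 2 the scope includes self-reported sun exposure, sun-protection behaviours, perceived risk, worry and the MHI-5.

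The section Efficacy analyses says that all group comparisons "will adjust for baseline scores and randomised stratification factors". This points to baseline as a covariate, but Secondary efficacy analyses does not say whether baseline is a covariate or a response row in the mixed model.

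The primary outcome is handled differently: "An analysis of covariance (ANCOVA), adjusted for baseline values and all randomised stratification factors will be performed". The random-intercept model appears once more, in the dosimeter sensitivity analysis of about 240 participants, "using GLMMs with random intercepts to account for the repeated measures". Primary efficacy analysis describes the target of that analysis as the overall intervention effect.

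**The concern.** For a normal outcome with homogeneous residuals, a random intercept gives every response row the same variance and every pair of rows the same covariance. With baseline as a covariate, two rows per person remain. A single non-negative covariance between two rows restricts nothing. What is restricted is the residual variance, which must be the same at 1 and 12 months. The model-based standard error of the 12-month contrast therefore rests on the average of the two.

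The SAP gives reasons to doubt equality, and they pull in different directions. Follow-up 1 is timed from receipt of the booklets and follow-up 2 from baseline, so the visits are unequally spaced, and baseline may predict the nearer visit better. On the other hand, follow-up 2 falls at about the same time of year as baseline, and many items ask about the past month, so baseline may predict 12 months better. The first case makes the 12-month intervals too narrow and the second makes them too wide. At stake are the 12-month CI and P value of most continuous questionnaire outcomes, each tested at a nominal 5% without multiplicity adjustment.

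**Working it through.** **What the SAP supplies.** It gives no SD, correlation or standard error for the three-visit outcomes, so there is no figure on this point to reproduce. The only usable design figure is the sample size, from a geometric mean ratio "of 0.8, coefficient of variation 0.9, 80% power and" a 5% alpha. It reproduces: the SD of log SED is √ln(1 + 0.9²) = 0.770 and the difference is −ln 0.8 = 0.223. The exact t test first reaches 80% at 189 per arm per phenotype group (power 0.802), and 4 × 189 = 756, or 378 per phenotype group. That is ample for estimating a 2 × 2 or 3 × 3 covariance matrix.

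**Assumptions.** Normal outcome, complete data, baseline as a covariate with a visit-specific slope, arm-by-visit means, model-based standard errors. SDs are 1 at every visit unless stated. Correlations are r01 (baseline to 1 month), r12 (1 to 12 months) and r02 (baseline to 12 months). All are assumed values.

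**Formula.** Residual variances are v1 = 1 − r01² at 1 month and v12 = 1 − r02² at 12 months. The model uses (v1 + v12)/2 for both. Hence

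model SE / true SE = √[ (v1 + v12) / (2·v12) ], and type I error = 2·[1 − Φ(1.96 × ratio)].

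| r01 / r12 / r02 | v1 | v12 | mean | SE ratio | type I error |
|---|---|---|---|---|---|
| 0.80 / 0.65 / 0.60 | 0.360 | 0.640 | 0.500 | 0.884 | 8.32% |
| 0.70 / 0.55 / 0.50 | 0.510 | 0.750 | 0.630 | 0.917 | 7.24% |
| 0.65 / 0.60 / 0.55 | 0.5775 | 0.6975 | 0.6375 | 0.956 | 6.10% |
| 0.55 / 0.75 / 0.55 | 0.6975 | 0.6975 | 0.6975 | 1.000 | 5.00% |
| 0.55 / 0.40 / 0.55 | 0.6975 | 0.6975 | 0.6975 | 1.000 | 5.00% |
| 0.45 / 0.50 / 0.65 | 0.7975 | 0.5775 | 0.6875 | 1.091 | 3.25% |

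r12 does not enter the formula. What matters is whether baseline predicts the two visits equally well. A common baseline slope changes little (0.886 in the first row, 1.090 in the last).

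**Unequal SDs.** With all correlations 0.5 and a 12-month SD 20% larger, v1 = 0.75 and v12 = 1.44 × 0.75 = 1.08. The ratio is √(0.915/1.08) = 0.920 and coverage 92.9%. With the SD 20% smaller, v12 = 0.48, the ratio is √(0.615/0.48) = 1.132 and coverage 97.3%. A 10% change in SD gives 93.9% or 96.2%.

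**Simulation check.** The mixed model was fitted to 365 simulated null trials (n = 756; 0.70/0.55/0.50; baseline as covariate). The mean model SE was 0.0582 and the empirical SD 0.0635, a ratio of 0.917. Rejection was 7.9%, with a Monte Carlo error of √(0.079 × 0.921/365) = 1.4 points. This agrees with the closed form.

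**Baseline as a response row.** At 0.70/0.55/0.50 the ratio is 0.93 if baseline means are constrained equal. For a change-from-baseline contrast it is 0.91: √[(2 − 2 × 0.583)/(2 − 2 × 0.50)], where 0.583 is the mean correlation. With saturated arm-by-visit means and equal SDs, the raw 12-month difference has ratio 1.00, but that contrast is not adjusted for baseline as Efficacy analyses requires.

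**Effect averaged over both visits.** Write c for the covariance of the two residuals. The true variance of a person's average is (v1 + v12 + 2c)/4. Replacing v1 and v12 by their mean leaves the sum unchanged, so the ratio is 1.00.

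**The case against.** The strongest reply is that no error is demonstrated. The SAP gives no visit-specific SD or correlation, every ratio above rests on assumed values, the direction is unknown, and mild departures move the type I error by only about one point. Same-season measurement at baseline and 12 months could well make the intervals conservative. This is also a condensed article. Naming a random intercept does not exclude heterogeneous residuals or robust standard errors, which a fuller document might specify. All of this stands as a limit on how firmly the point can be put. It does not remove the point, because the article does name a model and presents it as the way the within-person correlation is handled, and that model is calibrated for the 12-month contrast only under a condition nobody has checked.

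Four stronger readings are tempting and are not supported:

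- **The 12-month standard errors are simply wrong.** They are miscalibrated only if residual variances differ between visits, and the SAP has no figure that shows this.
- **One correlation is imposed across all three visits.** That applies only if baseline is a response row, and the baseline-adjustment sentence points the other way.
- **Only equal correlations throughout give a 5% test.** With baseline as a covariate it is enough, given equal SDs, that baseline predicts both visits equally well.
- **The dosimeter sensitivity analysis suffers in the same way.** If its overall effect is the average over both visits, its standard error is correct with complete data.

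**Conclusion.** The point holds in a conditional form. For continuous outcomes measured three times, the stated model ties the 12-month CI and P value to a residual variance pooled over 1 and 12 months. Over the correlations tried, with equal SDs and baseline as a covariate, the model standard error is about 0.88 to 1.09 of the true one (type I error about 8.3% to 3.3%), and exactly right when the two residual variances agree. This assumes homogeneous residuals, model-based standard errors and complete data. The direction cannot be predicted from the SAP, so the planned intervals cannot be taken as conservative. The primary ANCOVA is unaffected, as are continuous outcomes measured at two time points, which also use ANCOVA. The issue concerns secondary outcomes and is modest in size, but it is worth correcting because the remedy costs almost nothing.

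**What to change.** Change Secondary efficacy analyses only:

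1. State that baseline enters as a covariate (or, if preferred, as a response with means constrained equal between arms).
2. For continuous outcomes measured at three time points, replace the random-intercept model by a linear mixed model with categorical visit, arm-by-visit and baseline-by-visit terms (plus the stratification factors already planned) and an unstructured within-person covariance, fitted by REML. Report the 12-month contrast from it.
3. Name the fallback: if the model does not converge, keep the random intercept and use sandwich standard errors.

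Cost: a sentence or two of text and a small change of code, with no new data. With two post-baseline rows the unstructured matrix has 3 parameters against 2 for the random intercept, one more. With baseline as a third row it has 6 against 2, four more. With about 378 evaluable participants per phenotype group that is a negligible loss, and if the variances prove equal the results will hardly differ from those of the present plan.
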